### Sample size

The sample size calculation is driven by the urinary sodium endpoint. Assuming a between-group difference of 20 mmol in 24-h urinary sodium excretion, a standard deviation of 30 mmol, two-sided α of .05, and 90% power, 96 patients are required. Allowing for approximately 10% incomplete endpoint ascertainment, the target sample size is 106 patients.

### Statistical analysis

Continuous variables will be summarized as mean (SD) or median (IQR), according to distribution. Categorical variables will be summarized as counts and percentages. Baseline comparisons will use Student's *t*-test or the Mann–Whitney *U* test for continuous variables and χ^2^ or Fisher’s exact test for categorical variables.

All analyses will follow the intention-to-treat principle. The co-primary endpoints will be compared between groups at the prespecified 24-h time point using mixed-effects regression models with centre included as a random effect. Secondary endpoints assessed repeatedly after randomization will be analysed using mixed-effects models with random effects for centre and patient, and treatment effects will be estimated across the relevant post-randomization visits. All models will be adjusted for a prespecified set of baseline covariates selected *a priori* on the basis of their established prognostic association with the natriuretic and diuretic response, independently of their observed between-group balance: log-transformed baseline NT-proBNP, baseline estimated glomerular filtration rate, baseline parenteral loop diuretic dose, prior heart failure hospitalization, and the Charlson Comorbidity Index. For secondary endpoints with a repeated-measures structure, treatment comparisons will be adjusted for multiplicity using the Šidák method. Given the modest sample size, the trial is designed as a proof-of-concept study; the prespecified covariate-adjusted model will constitute the primary analysis, with unadjusted estimates reported for transparency. Statistical significance will be defined as a two-sided *P* < .05. All analyses will be performed in Stata 19 by an independent statistician (MedStats Consulting, Reading, PA, USA)

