### Endpoints

The trial has two co-primary endpoints, both assessed at 24 h after randomization:

Change in body weight from baseline to 24 h.Total urinary sodium excretion during the first 24 h after randomization.

These endpoints provide complementary renal and clinical assessments of the early treatment response. Total 24-h urinary sodium excretion quantifies the natriuretic response. Body weight change was selected as a pragmatic, non-urine-based clinical measure that is routinely available in hospital and ambulatory practice and does not require complete timed urine collection.

Secondary endpoints include changes in lower limb circumference at 5 and 10 cm above the ankle at 24 and 72 h; changes in clinical congestion score at 24 and 72 h; changes in IVC diameter at 3, 24, and 72 h; change in NT-proBNP at 72 h; change in CA-125 at 15 ± 3 days; cumulative furosemide-equivalent dose during the first 72 h after randomization; and 30-day safety.

Safety endpoints include adverse events related to compression; symptomatic hypotension; electrolyte disturbances at 72 h (hyponatraemia <135 mmol/L, hypernatraemia >150 mmol/L, hypokalaemia <3.5 mmol/L, and hyperkalaemia >5.0 mmol/L); worsening renal function (doubling of serum creatinine, estimated glomerular filtration rate decline ≥50% from baseline, renal replacement therapy); worsening heart failure events; and all-cause mortality. Worsening heart failure events are defined as hospitalization for heart failure or an urgent heart failure visit requiring parenteral diuretic therapy in an unscheduled ambulatory clinic or emergency department visit without an overnight stay. Recurrent episodes are counted separately when separated by at least 14 days of clinical stability; events occurring during the same hospitalization or continuous episode of care are counted as one event.

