### Trial status and baseline phenotype

Recruitment is complete. Of 108 patients who provided written informed consent, 2 were screening failures: one because of an ankle–brachial index <0.9 and one because of an IVC diameter >21 mm. A total of 106 patients were randomized, 54 to sham compression plus standard care and 52 to active compression plus standard care. All 106 patients were included in the 24-h body weight analysis population; 99 patients had evaluable 24-h urinary sodium data after exclusion of invalid urine collections. Participant flow is shown in *Figure 3*.

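### The article claims intention-to-treat for all analyses, but the sodium co-primary as written is a covariate-adjusted complete-case analysis of 99 of 106 randomized patients

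*Protocol article*

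**What the plan says.** Four statements in the protocol article bear on this point.

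- **Principle** (Statistical analysis): "All analyses will follow the intention-to-treat principle". No endpoint is exempted.
- **Endpoint** (Endpoints): the sodium co-primary is "Total urinary sodium excretion during the first 24 h after randomization", which is one post-randomization value per patient.
- **Model** (Statistical analysis): the co-primaries are "compared between groups at the prespecified 24-h time point using mixed-effects regression models with centre included as a random effect", adjusted for log NT-proBNP, eGFR, parenteral loop diuretic dose, prior heart failure hospitalization and the Charlson index. Patient-level random effects are mentioned only for secondary endpoints measured repeatedly.
- **Populations** (Trial status and baseline phenotype): "A total of 106 patients were randomized, 54 to sham compression plus standard care and 52 to active compression plus standard care". For weight, "All 106 patients were included in the 24-h body weight analysis population". For sodium, "99 patients had evaluable 24-h urinary sodium data after exclusion of invalid urine collections".

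The Sample size section sizes the trial on sodium and allows for about 10% of patients without a complete endpoint.

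**The concern.** The two co-primaries rest on different sets of patients, yet the article claims one principle for both. Seven randomized patients leave the sodium comparison because of a judgement made after randomization, on the same urine collection that yields the endpoint. Once that value is set aside, nothing in the stated model puts the patient back.

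What is at stake is how the result is described and how far it can be trusted. Sodium drives the sample size. A reader told that the analysis is intention-to-treat will assume that the comparison covers everyone randomized. If the exclusions are uneven between arms and the excluded patients truly differ in natriuresis, the estimated difference is off by an amount that the 99-patient analysis cannot reveal.

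**Working it through.** **1. The plan's own figure.** Inputs from Sample size: "Assuming a between-group difference of 20 mmol in 24-h urinary sodium excretion", SD 30 mmol, two-sided alpha 0.05, power 90%.

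n per arm = 2 × (1.960 + 1.282)² × 30² / 20² = 47.3, rounded up to 48, so 96 in total. This matches the article. Inflation gives 96 × 1.10 = 105.6, so 106, or 96 / 0.90 = 106.7, so 107. The stated 106 reproduces within rounding convention.

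**2. The loss.** 106 − 99 = 7, and 7/106 = 6.6%. This is below the planned 10%.

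**3. Power at 99.** For a 50/49 split, SE = 30 × √(1/50 + 1/49) = 6.03 mmol. Power = Φ(20/6.03 − 1.960) = Φ(1.356) = 91%. With the t distribution and splits from 54/45 to 50/49, power is 90.5% to 90.7%. With all 106 it would be 92.5%.

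**4. What the model can recover.** There is one outcome per patient, one time point and a centre random effect. A patient with no sodium value contributes no term to the likelihood. The model therefore estimates the covariate-adjusted difference among patients with a valid collection. It is unbiased for the full randomized comparison if, given arm and the model covariates, being excluded is unrelated to true sodium output.

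**5. Possible bias, before covariate adjustment.** Let a and b be the exclusions in the active arm (52) and the sham arm (54). Let D be the amount by which true sodium output in kept patients exceeds that in excluded patients, taken as equal in both arms. Then

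bias = (a/52 − b/54) × D.

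The text gives neither the split nor D. As assumptions, D = 30 mmol (1 SD) and 60 mmol (2 SD):

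| Active:sham | a/52 − b/54 | D = 30 | D = 60 |
|---|---|---|---|
| 7:0 | 0.135 | 4.0 | 8.1 |
| 6:1 | 0.097 | 2.9 | 5.8 |
| 5:2 | 0.059 | 1.8 | 3.6 |
| 4:3 | 0.021 | 0.6 | 1.3 |
| 3:4 | −0.016 | −0.5 | −1.0 |
| 0:7 | −0.130 | −3.9 | −7.8 |

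Values are in mmol. For scale, the design effect is 20 mmol, and the smallest difference reaching significance is about 1.96 × 6.03 = 11.8 mmol.

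If the gap ran in opposite directions in the two arms, even a 4:3 split could give (4/52 + 3/54) × 60 = 7.9 mmol. Nothing in the article suggests such a pattern.

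**6. How likely the extremes are.** If exclusion were unrelated to arm, the chance that all 7 fall in the active arm is C(52,7)/C(106,7), about 0.5%. For either arm it is about 1.3%.

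**The case against.** The case against has real weight.

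- **A missing outcome does not by itself breach intention-to-treat.** Patients can be kept in their assigned arm with a value missing, and the article planned for and disclosed the loss. This stands as far as it goes. But the article says that all analyses follow the principle, reports collections already rejected, and states a model that cannot use those patients.
- **The full analysis plan may handle the 7.** It may, and the lack of an imputation method or validity rule in a condensed article is not the complaint. The point is that the two statements printed here do not fit together. If a method covering all 106 exists, one sentence settles the matter.
- **Adjusted complete-case analysis is defensible at 6.6% missing.** This stands. It is valid if exclusion depends only on arm and the covariates, and the relevant D is what remains after adjustment. That is a reason to name the analysis correctly and test it, not to call it something else.
- **Weight is a weak predictor of sodium.** The Discussion itself warns that weight change does not track diuresis one for one. So imputation using weight adds some information but is no cure.

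A reader might also infer that rejecting invalid collections trims poor responders. The article does not support that. Under-collected urine gives a falsely low reading, and removing it removes measurement error. It does not show that those patients truly excreted less. Nor does the text suggest that rejection depended on arm: Randomization and blinding says that outcome assessors are blinded and that those who apply bandages are separate from urinary assessment. The split by arm may be in Figure 3, which is not visible here.

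**Conclusion.** The mismatch is real and limited. As written, the sodium co-primary is a covariate-adjusted complete-case analysis of 99 of 106 randomized patients, under an unqualified intention-to-treat label. Power is unaffected.

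Bias is possible but not demonstrated. With a common gap of 30 to 60 mmol in true output it is negligible for a near-even split (about 0.6 to 1.3 mmol at 4:3 active:sham). It becomes material, at about 4 to 8 mmol, only when all 7 are in one arm, which would be unlikely by chance. These figures rest on an assumed gap and an unknown split, and covariate adjustment could reduce them.

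It would be wrong to conclude that the sodium result is already biased or that the trial is underpowered. This is a should-fix.

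**What to change.** 1. **Relabel.** Describe the 99-patient sodium analysis as randomized patients with a valid collection, analysed as complete cases, and limit the intention-to-treat statement accordingly.
2. **Add an analysis of all 106 as randomized.** Either multiply impute the 7 sodium values by arm, using 24-h weight change and the model covariates, or model sodium and weight jointly. Weight is held for every patient. Complete baseline covariates for the 7 are likely but not stated, and should be checked.
3. **Add a delta-adjusted tipping-point analysis.** Imputation under missing-at-random does not address exclusion related to the outcome. Shifting the imputed values by arm shows how large a departure would change the conclusion.
4. **Report the 7 exclusions by arm.** This alone shows where in the table above the trial lies.

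The cost is a few lines of wording and a few days of programming on data already held, best settled before the treatment comparison is seen. The downside is an added modelling assumption, which is small and visible if the complete-case result is shown beside it.

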**Methods:**

COMPRESSION-HF (NCT06418932) is an investigator-initiated, multicentre, randomized, double-blind, sham-controlled trial in which adults with ADHF, bilateral leg oedema (grade II or higher of IV), N-terminal pro–B-type natriuretic peptide (NT-proBNP >1000 pg/ml), and IVC diameter ≤21 mm were assigned 1:1 to active bilateral lower limb compression (two-layer inelastic–elastic bandaging; manufacturer-specified nominal ankle pressure, approximately 20 mm Hg) plus parenteral furosemide or to sham bandaging plus parenteral furosemide, for up to 72 h. The two co-primary endpoints are 24-h urinary sodium excretion and change in body weight from baseline. Secondary endpoints include changes in lower limb circumference, clinical congestion score, and IVC diameter, together with NT-proBNP at 72 h, cumulative 72-h furosemide-equivalent dose, carbohydrate antigen 125 (CA-125) at day 15 ± 3, and 30-day safety. Continuous endpoints will be analysed with mixed-effects analysis of covariance or repeated-measures models including centre as a random intercept. Recruitment is complete (106 patients randomized); the trial was powered to detect a 20 mmol between-group difference in 24-h urinary sodium excretion.

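### Repeated secondary endpoints: the patient random effect, as ordinarily fitted, gives every visit the same variance; a visit-specific covariance should be fixed before unblinded analysis

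*Protocol article*

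**What the plan says.** The Statistical analysis section of the protocol article gives one approach for every secondary endpoint with repeated measurements: "mixed-effects models with random effects for centre and patient, and treatment effects will be estimated across the relevant post-randomization visits". It adds that for these endpoints "treatment comparisons will be adjusted for multiplicity using the Šidák method". It does not describe the residual covariance or mention treatment-by-visit terms.

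The Endpoints section shows which endpoints this covers:

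- "changes in IVC diameter at 3, 24, and 72 h" (three visits, and the only endpoint with a 3-h measurement);
- "changes in lower limb circumference at 5 and 10 cm above the ankle at 24 and 72 h" (two visits);
- "changes in clinical congestion score at 24 and 72 h" (two visits).

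NT-proBNP, CA-125 and cumulative furosemide-equivalent dose are each listed at a single time.

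The Methods paragraph of the abstract describes the continuous analyses as "mixed-effects analysis of covariance or repeated-measures models including centre as a random intercept". It calls only the centre term a random intercept and does not mention a patient term.

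**The concern.** A patient random intercept with independent, equal-variance residuals is compound symmetry: each visit has the same variance and each pair of visits the same correlation. The model then estimates one pooled variance and uses it for the treatment comparison at every visit. When spread differs between visits, that pooled figure is wrong at each visit that departs from the average.

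Per-visit comparisons appear to be intended. The endpoints are defined at named times, and a Šidák adjustment within a repeated-measures endpoint most naturally counts visits. Šidák corrects for the number of comparisons but does not repair a standard error that is wrong for a given visit.

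The comparison most exposed is IVC diameter at 3 h. The Introduction and Discussion rest the refill hypothesis on an early rise in IVC diameter after compression. If change is less variable at 3 h than at 72 h, the 3-h interval would be too wide and the 72-h interval too narrow, so the mechanistic test would lose power while the late test became too liberal.

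**Working it through.** **Plan's own figures.** The article states no figure for the repeated endpoints. Its sample size does not use this model and reproduces: 2 × (1.960 + 1.282)² × (30/20)² = 47.3, so 48 per arm and 96 in total; 96 × 1.10 = 105.6, so 106.

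**Inputs from the article.** 54 sham and 52 active patients; IVC at three visits, the other two endpoints at two; two-sided 5%; Šidák adjustment.

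**Assumed inputs, not in the article.** SDs of IVC change of 2.0, 2.5 and 3.0 mm at 3, 24 and 72 h; correlations of 0.6 (3 with 24 h), 0.3 (3 with 72 h) and 0.6 (24 with 72 h); complete data; no centre effect or covariates.

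**Step 1: pooled against true standard error.** With balanced data and treatment-by-visit terms, compound symmetry uses the mean visit variance everywhere.

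- Mean variance = (2.0² + 2.5² + 3.0²)/3 = 19.25/3 = 6.417, so pooled SD = 2.533 mm.
- Allocation factor = √(1/52 + 1/54) = 0.1943.
- Model SE at every visit = 2.533 × 0.1943 = 0.492 mm.
- True SEs = 0.389, 0.486 and 0.583 mm.
- Ratio r of model to true SE = 1.27, 1.01 and 0.84.

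**Step 2: type I error per visit** = 2 × [1 − Φ(z × r)].

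The Šidák level for three visits is 1 − 0.95^(1/3) = 1.70%, so z = 2.388.

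| Visit | r | Error at nominal 5% (z = 1.960) | Error at Šidák 1.70% (z = 2.388) |
|---|---|---|---|
| 3 h | 1.27 | 1.3% | 0.2% |
| 24 h | 1.01 | 4.7% | 1.6% |
| 72 h | 0.84 | 9.8% | 4.4% |

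Family-wise error over the three Šidák-adjusted comparisons, by simulation with these correlations, is about 5.6 to 5.7%, against 4.4% when the SDs are equal.

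**Step 3: range over assumed SDs.**

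| Assumed SDs (mm) | r at 3/24/72 h | Error at nominal 5% | Error at Šidák 1.70% |
|---|---|---|---|
| 2.0/2.0/2.0 | 1.00/1.00/1.00 | 5/5/5% | 1.7/1.7/1.7% |
| 2.0/2.5/3.0 | 1.27/1.01/0.84 | 1.3/4.7/9.8% | 0.2/1.6/4.4% |
| 2.0/3.0/4.0 | 1.55/1.04/0.78 | 0.2/4.2/12.8% | 0.02/1.3/6.4% |

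For a two-visit endpoint with a 72-h to 24-h SD ratio of 1.5, r = 1.27 and 0.85, giving about 1.2% and 9.6% at nominal 5%.

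**Step 4: check by fitting the model.** A REML random-intercept model with visit and treatment-by-visit terms was fitted to 300 simulated trials of 54 and 52 patients per scenario, with correlations of 0.7, 0.4 and 0.6.

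- SDs 2/2.5/3: SE ratios 1.30, 1.00 and 0.86; coverage of 95% intervals 99.7%, 93.7% and 92.0%.
- Equal SDs: SE ratios 1.03 to 1.06; coverage 94.3% to 96.7%. Unequal correlation alone therefore does essentially no harm to per-visit comparisons with complete data.

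**Step 5: effect averaged over visits.** With the Step 1 SDs and assumed correlations, the three covariances are 3.0, 1.8 and 4.5 (mean 3.1).

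- True variance of a patient's mean over visits = [19.25 + 2 × (3.0 + 1.8 + 4.5)]/9 = 37.85/9 = 4.206.
- Compound symmetry = (3 × 6.417 + 6 × 3.1)/9 = 4.206.

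The two agree, so an averaged effect is not distorted when data are complete.

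**The case against.** The strongest reply is that the article does not say what the criticism needs. It never says that the patient term is only an intercept and gives no residual covariance, and a patient random effect does not exclude visit-specific residual variances. Covariance structure is also a detail that an article often leaves to the analysis plan, which is not shown. This stands against any claim that the plan fixes compound symmetry outright. It does not remove the point, because the article does name a within-patient structure, and the ordinary way to fit what it names yields a common variance. An unstructured covariance is not normally described this way, since a patient intercept added to it is not separately identifiable.

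Several stronger readings are tempting, and the documents do not support them:

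- A reader might infer that the per-visit intervals are wrong as a matter of fact. That needs unequal visit variances, and the article reports no visit-specific SD.
- A reader might object both to the standard errors and to mixing early refill with later decongestion. The two cannot both hold for one analysis. If effects are per visit, nothing is mixed; if one effect is averaged over visits, its standard error is right with complete data. In the second case only the choice of target is open to question.
- A reader might extend the point to the co-primary models, or to large-sample inference in them. Those are single 24-h comparisons, and the article does not state the estimation method.
- A reader might quote the 10% error at 72 h as the rate of false claims. The plan applies Šidák, and after that adjustment the chance of any false claim for the endpoint stays near nominal, at about 5.7%. What remains is an uneven split between visits.

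**Conclusion.** The concern holds in a conditional form and is limited to three secondary endpoints in a declared proof-of-concept trial. The model described would, as ordinarily fitted, impose a common variance across visits. If spread grows with time, early comparisons are too conservative and late ones too liberal. Under SDs of 2.0/2.5/3.0 mm the 3-h IVC interval is 27% too wide and the 72-h interval 16% too narrow. The Šidák-level error at 72 h rises from 1.7% to 4.4%, while at 3 h it falls to 0.2%. These sizes rest wholly on assumed SDs and on per-visit reporting, and with equal SDs the effect disappears. The 3-h visit concerns IVC diameter alone. It is worth changing because the alternative is safe whether or not the variances differ, and the model can still be fixed before results are seen: recruitment is complete and the article describes the analyses as still to come.

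**What to change.** Before unblinded analysis, specify for the repeated secondary endpoints (or confirm that the analysis plan already does so):

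- an unstructured within-patient residual covariance, so that each visit has its own variance, in place of the patient random intercept;
- the centre random intercept, retained;
- treatment-by-visit and baseline-value-by-visit terms, with the planned covariates;
- REML estimation with small-sample degrees of freedom, such as Kenward–Roger;
- treatment effects reported per visit, with IVC diameter at 3 h shown separately, and the Šidák adjustment applied across those visit comparisons.

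The cost is one model statement and a few extra parameters: 3 covariance parameters for two visits (2 × 3/2) and 6 for three (3 × 4/2), which 106 patients support readily. No change is needed to the co-primary analyses, the sample size or data collection.

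### The single covariate list for all models leaves out the outcome's own baseline for the body-weight co-primary and four of the five secondary change endpoints

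*Protocol article*

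**What the plan says.** The Statistical analysis section of the protocol article states that "All models will be adjusted for a prespecified set of baseline covariates", and names them: "log-transformed baseline NT-proBNP, baseline estimated glomerular filtration rate, baseline parenteral loop diuretic dose, prior heart failure hospitalization, and the Charlson Comorbidity Index". They were chosen for their prognostic link with the natriuretic and diuretic response. The section then gives this model its status: "the prespecified covariate-adjusted model will constitute the primary analysis, with unadjusted estimates reported for transparency".

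Under Endpoints, one co-primary is a post-randomization total with no baseline counterpart: "Total urinary sodium excretion during the first 24 h after randomization". The other is a change: "Change in body weight from baseline to 24 h". Five secondary endpoints are changes too: limb circumference ("Secondary endpoints include changes in lower limb circumference at 5 and 10 cm above the ankle at 24 and 72 h"), congestion score and IVC diameter ("changes in clinical congestion score at 24 and 72 h; changes in IVC diameter at 3, 24, and 72 h"), NT-proBNP at 72 h, and CA-125 at about day 15.

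The abstract describes the models more loosely: "Continuous endpoints will be analysed with mixed-effects analysis of covariance or repeated-measures models including centre as a random intercept".

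**The concern.** For an endpoint defined as a change, the outcome's own baseline is usually among its strongest predictors, and it is already measured because the change cannot be computed without it. A list built around natriuresis does not supply it for limb circumference, congestion score, IVC diameter, CA-125 or body weight.

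Two things are at stake. The first is precision, in a trial that its authors call modest in size and proof of concept. The second is chance imbalance: if the arms differ at baseline on the outcome, a change score that is not adjusted for that baseline carries part of the difference into the treatment estimate.

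The document gives some reason to expect dependence on baseline. In the pilot study described in the Introduction, IVC diameter rose by 2.4 mm in patients with a baseline of 21 mm or less and by 0.8 mm in those above. The trial enrols only the lower range, so this is no more than indicative.

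**Working it through.** **1. The plan's own figure.** Inputs from the Sample size section: difference 20 mmol, SD 30 mmol, two-sided alpha 0.05, power 90%.

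n per arm = 2 × (1.960 + 1.282)² × (30/20)² = 2 × 10.51 × 2.25 = 47.3, rounded up to 48, so 96 in total. Adding 10% gives 96 × 1.10 = 105.6, or 106. (Dividing by 0.90 gives 107.) The stated 96 and 106 are reproduced. They rest on urinary sodium, so nothing below changes them.

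**2. Which endpoints have their own baseline in the list.**

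| Endpoint | Defined as change? | Own baseline in list? |
|---|---|---|
| 24-h urinary sodium (co-primary) | No | Not applicable |
| Body weight (co-primary) | Yes | No |
| Limb circumference | Yes | No |
| Congestion score | Yes | No |
| IVC diameter | Yes | No |
| NT-proBNP | Yes | Yes (log) |
| CA-125 | Yes | No |

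**3. Precision.** Let s0 and s1 be the baseline and follow-up SDs, rho their correlation, and b = rho × s1/s0 the slope.

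- Variance of the change: s0² + s1² − 2 × rho × s0 × s1.
- Variance after adjusting for baseline: s1² × (1 − rho²).
- Difference, that is, the variance removed: s0² × (1 − b)².
- With s0 = s1, adjusted variance / change variance = (1 + rho)/2.

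The documents give no rho, so a range is assumed. The power column supposes that the change-score analysis has 80% power: power = Phi[(1.960 + 0.842)/√ratio − 1.960].

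| Assumed rho | Variance ratio | Variance removed | Power, from 80% |
|---|---|---|---|
| 0.3 | 0.65 | 35% | 93.5% |
| 0.5 | 0.75 | 25% | 89.9% |
| 0.7 | 0.85 | 15% | 86.0% |
| 0.9 | 0.95 | 5% | 82.0% |
| 0.99 | 0.995 | 0.5% | 80.2% |

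These percentages are reductions in variance. As effective sample size, 15% and 35% correspond to 1/0.85 − 1 = 18% and 1/0.65 − 1 = 54%. All are upper guides, because the five listed covariates may already explain part of the same variance. For IVC diameter the entry cut-off of 21 mm shrinks s0 while leaving b unchanged, so s0² × (1 − b)² is smaller and the gain is likely lower.

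**4. Chance imbalance.** With 54 and 52 patients (Trial status), the standard error of a baseline difference is √(1/54 + 1/52) = 0.194 SD. With equal variances, a change score carries (1 − rho) of any such difference into the estimate. For a one-standard-error imbalance:

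- rho 0.3: 0.7 × 0.194 = 0.136 SD
- rho 0.5: 0.5 × 0.194 = 0.097 SD
- rho 0.7: 0.3 × 0.194 = 0.058 SD

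**5. Body weight at 24 h.** Weights one day apart are almost perfectly correlated. Assume rho 0.98 to 0.998 and a weight SD of 12 to 18 kg. The variance removed is (1 − rho)/2, so 1% at 0.98 and 0.1% at 0.998. The bias from a one-standard-error imbalance runs from 0.002 × 12 × 0.194 = 0.005 kg to 0.02 × 18 × 0.194 = 0.07 kg.

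**The case against.** Four stronger readings are tempting, and the document does not support them.

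- **That the abstract is contradicted, or that these are raw change-score models.** A model with treatment, centre and five baseline covariates is an analysis of covariance. The abstract's label leaves open whether the outcome's own baseline is included; it does not conflict with the Statistical analysis section.
- **That the IVC cut-off biases the comparison through regression to the mean.** The cut-off applies to both arms before randomization, so any regression to the mean is equal in expectation. Only chance imbalance could matter, and Table 2 shows mean IVC diameter of 18.0 mm and a median congestion score of 3 in both arms. Baseline weight and circumference are not reported there.
- **That the weight co-primary loses 4% to 16% of its precision.** This needs a correlation of 0.2 to 0.4 between baseline weight and weight loss, which the document does not give. With equal variances it would require rho of 1 − 2 × 0.04 = 0.92 down to 1 − 2 × 0.16 = 0.68, low for weights a day apart.
- **That baseline adjustment can never cost precision.** This is a large-sample result. When the slope is close to 1, as for 24-h weight, estimating one more coefficient among 106 patients can cost about as much as it gains.

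A further defence is that an article is condensed and endpoint-specific terms belong in the statistical analysis plan. That would hold if the article were silent. Instead it names a full list, applies it to all models and makes the result primary, so it states a choice. A separate plan that adds baseline terms would depart from the published text, and the two would need reconciling.

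**Conclusion.** The point holds as a weakness in a stated analysis choice. The outcome's own baseline is absent from the primary model for the body-weight co-primary and for four of the five secondary change endpoints.

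The consequence falls mainly on limb circumference, congestion score, IVC diameter and CA-125. If rho lies between 0.3 and 0.7 and the variances are equal, the variance given up is roughly 35% to 15%, less whatever the five covariates already explain, and probably less again for IVC diameter. For 24-h weight the precision gain is small, about 1% or less if rho is at least 0.98; there the case rests on consistency and on protection against imbalance. Urinary sodium and the sample size are untouched. The comparison remains valid under randomization without the change, so this is an improvement at very little cost and not the correction of an invalid analysis.

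**What to change.** Extend the covariate sentence in Statistical analysis with: *and the baseline value of the outcome for every endpoint expressed as change (log scale for CA-125), with a baseline-by-visit term in repeated-measures models.* Reword the abstract so that it says the same.

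The values are already collected. The cost is about one degree of freedom in a single-time-point model. With the interaction it is one coefficient per visit: two for circumference and congestion score, three for IVC diameter.

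Recruitment is complete and Table 2 already shows baseline data by arm. The change should therefore be made as a dated amendment before unblinding of outcomes, and justified by the general rule that a change is adjusted for its own baseline, not by any observed difference between the arms.
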